## Abstract

**Background:**

Ankle fractures are common. Management of ankle fractures generally involves a period of immobilisation followed by rehabilitation to reduce pain, stiffness, weakness and swelling. The effects of a rehabilitation program are still unclear. However, it has been shown that important components of rehabilitation programs may not confer additional benefits over exercise alone. The primary aim of this trial is to determine the effectiveness and cost-effectiveness of an exercise-based rehabilitation program after ankle fracture, compared to advice alone.

**Methods/Design:**

A pragmatic randomised trial will be conducted. Participants will be 342 adults with stiff, painful ankles after ankle fracture treated with immobilisation. They will be randomly allocated using a concealed randomisation procedure to either an *Advice *or *Rehabilitation *group. Participants in the *Advice *group will receive verbal and written advice about exercise at the time of removal of immobilisation. Participants in the *Rehabilitation *group will be provided with a 4-week rehabilitation program that is designed, monitored and progressed by a physiotherapist, in addition to verbal and written advice. Outcomes will be measured by a blinded assessor at 1, 3 and 6 months. The primary outcomes will be activity limitation and quality-adjusted life years.

**Discussion:**

This pragmatic trial will determine if a rehabilitation program reduces activity limitation and improves quality of life, compared to advice alone, after immobilisation for ankle fracture.

## Background

Ankle fracture, fracture of the distal tibia and/or fibula, is the second most common ankle injury after ankle sprain [1]. The incidence of ankle fracture is at least 5 per 10,000 person-years across all ages [2,3], but is higher in young men (13 to 28 per 10,000 person-years) and older women (16 to 20 per 10,000 person-years). The orthopaedic management depends on the severity of the fracture, but generally involves immobilisation of the ankle in a cast or a brace for about 6 weeks [4]. Surgical fixation is required in about 50% of cases [5,6].

The disabling sequelae of ankle fracture and the subsequent immobilisation frequently affect people's ability to return to work and sport. Our recent study showed that people with ankle fracture had significant activity limitation after the period of immobilisation (mean Lower Extremity Functional Scale score of 33.6, where no activity limitation receives a score of 80) and one-third were unable to walk without crutches [5]. Impairments include pain [5,6], stiffness [7,8], weakness [9-11] and swelling [12,13]. Rehabilitation programs are often provided to address these sequelae and can commence as soon as the fracture has been stabilised (i.e. during the period of immobilisation) or, more often, after the period of immobilisation (i.e. when bone union has occurred). Typically a post-immobilisation program consists of stretch, manual therapy, exercise, gait training and advice [5,6].

There is limited evidence on the effects of rehabilitation interventions for ankle fracture. A Cochrane systematic review has evaluated the effects of rehabilitation interventions applied during or after the period of immobilisation. It concluded that commencing weight bearing during the immobilisation period and wearing a brace that can be removed to allow gentle ankle exercise may improve outcome after ankle fracture [14].

The Cochrane review identified only two randomised controlled trials which investigated effects of rehabilitation after the immobilisation period [6,15]. Two other trials have been recently completed [5,16]. These trials concluded that adding passive stretch or manual therapy to an exercise program does not improve clinical or economic outcomes compared to exercise alone [5,6,15], and found no overall benefit of participating in an exercise program [16]. However, in the trial that compared an exercise program to usual care, benefits of the exercise program could have been underestimated as there was a high uptake of physiotherapy (a mean of 7 physiotherapy appointments) by participants from the usual care group [16]. In addition, the trial only included people whose ankle had been treated surgically [16].

It is still unclear if some sub-groups could benefit more from rehabilitation than others. Nilsson et al [16] compared the effects of rehabilitation on Olerud-Molander Ankle Score (range 0 to 100) in those aged < 40 years and those ≥ 40. There was no difference in effects of rehabilitation at 6 months. However the effect of rehabilitation at 12 months was greater in people aged < 40 than in those aged ≥ 40 (mean difference in effect 16.9 points, 95% CI 5.6 to 28.2). This finding should be considered provisional until it is replicated in other studies. We postulate that participation in a rehabilitation program may particularly benefit older women (aged over 50 years) as they are more likely to suffer from osteoporosis [17], and physical performance [18] and physical activity [19] also decline with age. The severity of fracture has also been found to influence outcome in ankle fracture [20], which raises the idea that rehabilitation should be offered selectively. In this case, it could be argued that people with more severe fracture would have worse outcomes and, consequently, would benefit more from a rehabilitation program.

The prediction of outcome after ankle fracture is relatively imprecise. We have previously shown that out of eight variables, pain and dorsiflexion range of motion soon after the period of immobilisation were the only independent predictors of outcome, but explained only 9 to 12% of the variance in activity limitation in the short- to medium-term [21]. Other variables (e.g. psychological factors) may be better predictors of outcome after ankle fracture. It has been shown that psychological variables (including pain catastrophising and depression) appear to be important predictors of outcome in people with other musculoskeletal conditions [22]. This issue has not been examined after ankle fracture.

The primary aims of the trial to be conducted are, therefore, to determine (a) the effectiveness and cost-effectiveness of rehabilitation, compared to simple advice and (b) if effects of rehabilitation are influenced by fracture severity or by the age and gender of participants. A secondary aim is to identify predictors of outcome after ankle fracture.

## Methods/Design

The trial will be an assessor-blinded pragmatic randomised controlled trial. Three hundred and forty two participants will be randomly allocated to one of two groups: an *Advice *group and a *Rehabilitation *group (~171 in each group). Outcomes will be assessed at baseline, 1, 3 and 6 months by a blinded assessor (Figure 1).

**Figure 1 F1:**
[figure not shown]
**Experimental protocol**.

### Participants

Participants will be recruited from four hospitals. The inclusion criteria will be:

• ankle fracture treated with immobilisation (e.g. cast, brace), with or without surgical fixation

• immobilisation removed on the day of recruitment

• approval received from orthopaedic specialist to weight-bear as tolerated or partial weight-bear

• reduced ankle dorsiflexion range of motion (at least 30 mm less motion compared to the non-fractured leg using the weight-bearing lunge method) [23]

• at least 2 out of 10 pain in the ankle when up to 50% of body weight is borne through the affected leg

• completed skeletal growth (i.e. no evidence of epiphyseal cartilage in the tibia in x-rays taken for fracture management)

• no concurrent pathologies (e.g. symptomatic osteoarthritis, stroke, other fractures) which affect the ability to perform everyday tasks or the measurement procedures used in this trial, and

• informed consent obtained.

### Recruitment sites

Participants will be recruited from the fracture clinics of four public hospitals in Sydney, Australia: Royal North Shore Hospital, Prince of Wales Hospital, Royal Prince Alfred Hospital and Ryde Hospital. Royal North Shore Hospital, Prince of Wales Hospital and Royal Prince Alfred Hospital are major teaching hospitals with more than 500 beds. Ryde Hospital is a smaller teaching hospital of close to 200 beds. At these hospitals the fracture clinics are staffed by physiotherapists, who are responsible for the application and removal of immobilisation and the provision of advice about rehabilitation after orthopaedic clearance.

### Randomisation

Randomisation will be conducted using a telephone-based randomisation service provided by the Australian National Health and Medical Research Council (NHMRC) Clinical Trials Centre. This ensures concealment of the allocation schedule. Allocation will be stratified by site and blocked within strata using random permuted blocks.

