### Statistical analysis

Analyses will be conducted by 'intention-to-treat' (i.e. all available data from all randomised participants will be analysed in the group to which the participant was allocated). Multiple imputation will be used for missing data. To test the effects of intervention on continuous outcomes (activity limitation, quality of life, return to pre-fracture work and leisure, physical activity (metabolic equivalent minutes per week), ankle range of motion, pain, walking speed, and global perceived effect of treatment), between-group comparisons will be conducted using longitudinal mixed models [30,31]. The independent variables will be a dummy-coded variable indicating group membership, the time at which the measurement was taken (four times, dummy-coded as three variables, with the baseline time as the referent category), and the three time-by-group interactions. The effect of rehabilitation at each of the three follow-up time points is estimated with the relevant interaction term. The model will incorporate random intercepts to account for the dependence of repeated measures. Survival analysis will be used to estimate between-group differences in days to pain-free walking and days to return to full pre-fracture work. Odds ratios will be calculated for physical activity (level), satisfaction with trial treatment, and adverse events.

In a second analysis, designed to test the influence of fracture severity on treatment response, additional terms (fracture severity and the interactions of fracture severity with the group and time variables) will be entered into the model. The effect of fracture severity on treatment response will be determined by examining the interactions between group membership, fracture severity and the time variables. A similar analysis will test the influence of participant age and gender on treatment response. Participants will be divided into women aged over 50 and others. Again, additional terms (age/gender and the interactions of age/gender with the group and time variables) will be entered into the model. The effect of age/gender on treatment response will be determined by examining the interactions between group membership, age/gender and the time variables.

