The primary conclusions about effectiveness of rehabilitation will be based on between-group comparisons of activity limitation and quality of life at 3 months. The primary conclusions about whether fracture severity and age and gender influence the effectiveness of intervention will be based on the interactions between these factors and effects of rehabilitation for activity limitation and quality of life at 3 months.

The economic evaluation will examine differences between participants in the *Rehabilitation *and *Advice *groups in terms of costs incurred and changes in perceived activity limitation (cost-effectiveness analysis) or utility gained (cost-utility analysis). The incremental cost-effectiveness (utility) ratio (ICER) will be calculated as: ICER = (*C_R _*- *C_A_*)/(*U_R _*- *U_A_*), where C is average cost, U is the average effectiveness or utility score, and subscripts R and A denote the *Rehabilitation *and *Advice *arms. The *Rehabilitation *program can be said to be cost-effective relative to *Advice *about exercise if it (a) produces less activity limitation or greater utility at a lower cost or (b) the cost per activity limitation avoided or per quality-adjusted life years gained (i.e. the incremental cost-effectiveness (utility) ratio) is less than some threshold value (e.g. $50,000). Bias-corrected bootstrapped estimates (1,000 replications) will be used to test for the difference in mean costs and to obtain 95% confidence intervals for between-group differences in mean costs. Between-group differences in utilisation will be tested using Fisher's exact test. Sensitivity analyses will be undertaken to explore the robustness and validity of the results. Both costs and outcomes will be varied in line with results from similar studies reported in the literature and the upper and lower limits of estimates from this trial.

To establish the predictors of outcome after ankle fracture, univariate linear regression will be used to examine the relationship between seven baseline variables (fracture severity, pain, ankle range of motion, mobility, depression, anxiety and stress, and pain catastrophising) and activity limitation at 1-month and 6 months after removal of immobilisation. A multivariate linear prediction model will be developed using methods described by Harrell [32].

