### Sample size

A sample of 76 participants (38 per group) would provide an 80% probability of detecting a difference between the group means of 10 points on the 80-point Lower Extremity Functional Scale (assuming a SD of 15 points, based on data from our recently completed trials [5,6]). This sample size will also provide 80% probability of detecting a difference between the group means of 2.75 points on the 45-point Assessment of Quality of Life scale (assuming a SD of 4 points, based on data from our recently completed trial [5]). Effects smaller than these are unlikely to be considered clinically worthwhile. In our calculations we assumed an alpha of 0.05, and we allowed for 5% loss to follow-up. We conservatively ignored the extra precision conferred by the longitudinal design.

In order to power the trial for analyses of the interactions with fracture severity and age/gender of participants we need to inflate the sample size by a factor of 2 + *k *+ 1/*k*, where *k *is the sub-group ratio. We anticipate the sub-group ratio for both *severe*: *less severe *fracture and *women aged over 50*: *others *is ~1:2 (based on our recently completed studies [5,6]). Thus, a sample of 72 × 4.5 = 342 participants (171 per group) will be recruited.

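### Allocation is stratified by site, but the mixed model's listed terms omit site; the cost is a slightly wide standard error for the main effect if change from baseline differs between hospitals

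*Protocol article*

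**What the plan says.** Under Participants: "Participants will be recruited from four hospitals". Under Randomisation: "Allocation will be stratified by site and blocked within strata using random permuted blocks".

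The Statistical analysis section spells out the model for continuous outcomes. "The independent variables will be a dummy-coded variable indicating group membership, the time at which the measurement was taken" (four occasions, three indicators, "with the baseline time as the referent category), and the three time-by-group interactions"). It adds: "The model will incorporate random intercepts to account for the dependence of repeated measures". The estimator is also fixed: "The effect of rehabilitation at each of the three follow-up time points is estimated with the relevant interaction term". The main conclusions rest on "between-group comparisons of activity limitation and quality of life at 3 months".

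Site does not appear in this list. Nor does it appear in the second set of models, which add fracture severity or the age/gender grouping, or anywhere else in the analysis text. Table 1 schedules global perceived effect at the three follow-ups only, and the Statistical analysis section puts it in the same mixed model.

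**The concern.** Blocking within site balances the arms within each hospital, so differences between hospitals contribute almost nothing to the real sampling error of the treatment comparison. A model that does not know about site can leave those differences in its residual. It then reports a standard error larger than the true one, and the test runs a little below its nominal level. Precision gained by the design goes unused.

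This is not a detail deferred to another document, because the article writes the model's terms out one by one. It is plausible that recovery differs by hospital. Recruitment sites describes three large teaching hospitals and one much smaller one, and Interventions leaves further consultations, stretches and manual therapy to the physiotherapist. The article gives no estimate of such a difference.

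**Working it through.** **Inputs.** From Sample size: SD 15 and a target of "detecting a difference between the group means of 10 points on the 80-point Lower Extremity Functional Scale"; total 342 (171 per group). Assumed, because the article does not give them: within-person correlation ρ = 0.5 (range 0.3 to 0.7), site sizes 100/100/100/42, two-sided alpha, and the size of any hospital difference.

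**The plan's own figure.** 2 × (1.960 + 0.842)² × 15²/10² = 35.3, so 36 per arm. 36/0.95 = 37.9, so 38 per arm and 76 in total. 76 × (2 + 0.5 + 2) = 76 × 4.5 = 342. The total reproduces. The printed multiplication uses 72, which would give 324; that looks like a slip for 76 and does not affect this point.

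**Step 1: standard error of the stated estimator.** For a difference in change from baseline under random intercepts, SE = √(2 × 15² × (1 − ρ) × 4/342). This gives 1.92, 1.62 and 1.26 for ρ = 0.3, 0.5 and 0.7. No constant between-hospital variance enters the formula.

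**Step 2: hospitals differ by a constant amount.** The stated model was simulated (1,000 runs, complete data, ρ = 0.5) with a constant site SD of 4.7 points, about 10% of variance (4.7²/15² = 0.098). The mean model SE for the 3-month interaction was:
- no site term: 1.621
- site main effect: 1.621
- site and site-by-time: 1.622

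Type I error was 0.050 in each. With 5% of follow-up values missing, the SE was 1.650 in all three.

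**Step 3: hospitals differ in change from baseline.** The shift is assumed to be the same at all three follow-ups.

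| Site-by-time SD | No site term | Site main effect | Site and site-by-time | Excess without site-by-time |
|---|---|---|---|---|
| 3.35 points | 1.640 | 1.640 | 1.620 | 1.640/1.620 = 1.012 |
| 4.7 points | 1.662 | 1.662 | 1.623 | 1.662/1.623 = 1.024 |

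**Step 4: closed-form check.** A shift s present at three of four occasions has a within-person sum of squares of s²(3 − 9/4) = 0.75s² on 3 degrees of freedom, so it adds 0.25s² to the residual variance. That variance is 225 × 0.5 = 112.5.
- SD 3.35: √((112.5 + 2.81)/112.5) = 1.012
- SD 4.7: √((112.5 + 5.52)/112.5) = 1.024

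These agree with step 3. The same formula gives 0.9% and 1.7% at ρ = 0.3 (residual variance 157.5), and 2.1% and 4.0% at ρ = 0.7 (residual variance 67.5).

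**Step 5: effect on the test.** With ρ = 0.5, 2 × (1 − Φ(1.96 × 1.012)) is about 4.7% and 2 × (1 − Φ(1.96 × 1.024)) is about 4.5%. The simulated type I errors (0.040 to 0.061 over all scenarios, simulation error about 0.007) are too coarse to confirm or exclude a shift this small, so the direction rests on the algebra.

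**Step 6: global perceived effect.** With no baseline value there is no change contrast. A constant hospital difference then sits in the random-intercept variance and enters the standard error of the group comparison directly.

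**The case against.** The strongest case against the point is that it hardly matters. The estimator is a within-person contrast, so the most familiar kind of hospital difference drops out of it. The article offers no evidence that change differs by hospital: all four are public teaching hospitals in one city, with common eligibility criteria, exercise cards and trained therapists. Adjustment for stratification factors is also commonly set out in a statistical analysis plan, which is not shown here. Most of this stands, and it is why the point is minor. The last part stands only partly, because the article does not leave the model open: it lists the terms, and site is not one of them.

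Three stronger readings are tempting and are not supported.

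- *Any difference in outcome between hospitals makes the standard errors too large.* That describes a comparison at a single time point. The article plans a contrast with baseline, and step 2 shows no effect of a constant difference on it.
- *The subgroup-interaction tests also run below 5%.* Stratifying by site balances the arms within site, not within site-by-severity or site-by-age/gender cells, so it does not remove site variation from those contrasts. A simulation of the case most favourable to this reading (a single time point, site explaining 5% or 10% of variance, blocks of 4 and one-third severe, both assumed; 20,000 runs each) gave interaction type I errors of 5.1% and 5.0% with no site term.
- *The survival and odds-ratio analyses are also misspecified.* The article gives no covariate list for them, so nothing can be said to have been left out.

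**Conclusion.** The mismatch between design and analysis is real: site is stratified on and then absent from a fully listed model. Its consequence is confined to the main treatment effect and arises only if change from baseline differs between hospitals. The standard error is then about 1 to 2.5% too large, resting on assumed site-by-time SDs of 3.35 to 4.7 points, ρ = 0.5 and an equal shift at each follow-up. Over ρ = 0.3 to 0.7 the range is 0.9 to 4.0%. The error is on the conservative side, and there is no bias and no raised false-positive risk. For global perceived effect, a secondary outcome, a constant hospital difference is enough to widen the standard error. The point is a free improvement of minor severity.

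**What to change.** Add site (three indicators) and site-by-time (3 × 3 = 9 terms) as fixed effects to the mixed models, and say so in the analysis text before unblinding. A site main effect alone changes nothing for outcomes measured at baseline, as step 3 shows, so the site-by-time terms are the part that matters there.

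The cost is one sentence and 3 + 9 = 12 degrees of freedom, with 342 participants planned. Site is already recorded for randomisation. If the terms prove unnecessary, almost nothing is lost: the simulated SE was 1.622 against 1.621 when hospitals differed only by a constant, and 1.622 with or without the terms when they did not differ at all.

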### Interventions

Participants in the *Advice *group will be given advice in a single session in the fracture clinic, after removal of immobilisation and after consultation with the treating orthopaedic specialist. A physiotherapist will advise the participant to do exercises that involve ankle movement in non-weight-bearing positions and will explain how to perform these exercises and how to progressively reduce the use of walking aids. The participant will be given a handout that summarises this advice with text and figures.

Participants in the *Rehabilitation *group will receive the same advice but will also participate in an exercise program that is designed, monitored and progressed by a physiotherapist, with participants encouraged to perform a carefully structured exercise program at home. Three types of exercises will be prescribed: ankle mobility and strengthening exercises, stepping exercises, and exercises involving weight-bearing and balancing on the affected leg. These exercises are routinely prescribed after immobilisation for ankle fracture and were used in our recently completed trials [5,6]. Exercise cards have been developed to standardise the exercises used. Participants will also receive gait training and ongoing advice about returning to usual work and leisure activities. In keeping with the pragmatic orientation of the trial, participating physiotherapists will not be prevented from administering stretches or manual therapy. The rehabilitation program will be provided during two sessions in week one and in one session from weeks two to four; further consultations will be at the discretion of the physiotherapist. Participants will be discharged by their physiotherapist when they achieve their pre-fracture function, reach a plateau in their progress, or choose to discontinue the treatment.

When appropriate, participants in both groups will be instructed to use ice for pain relief and compression and elevation for management of swelling. A compression bandage will be provided if required. Treatments will be administered by registered physiotherapists who will be trained to provide the *Advice *and *Rehabilitation *interventions in accordance with the trial protocol.

